#### Tissue and blood collection for exploratory endpoints

##### Tissue collection

For each patient a formalin-fixed, paraffin-embedded (FFPE) tumor tissue block (archival or recent) or a minimum of 15 unstained slides of tumor sample (2–3 μm sections; slices must be recent and collected on slides provided by the sponsor) must be available for biomarker (PD-L1) evaluation as stated in the inclusion criteria. Biopsy should be excisional, incisional or core-needle. Fine-needle aspiration is insufficient. Tumor PD-L1 assessment for retrospective sub-group analysis will be performed centrally according to institutional standards using the PD-L1 IHC 28–8 pharmDx assay.

It will be at the discretion of the investigator to determine whether a re-biopsy of a patient is required. The decision to re-biopsy shall be based on clinical judgment and necessity and should follow local guidelines and standards. If a recent biopsy has been collected and submitted, submission of archival tissue, if available, is still highly encouraged. In cases where retrospective haematoxylin and eosin staining by the central lab determines insufficient amounts of tumor tissue for the biomarker analyses, additional archived tissue may be requested by the sponsor, if available. If a re-biopsy after progression under study treatment is performed, submission of this tumor material is highly valued.

##### Blood collection

Participation of patients in the biomarker program is voluntary and must be documented in the informed consent form.

Routine haematological analysis of red and white blood cells and platelets are part of the scheduled patient assessments under therapy and are not a specific part of the exploratory biomarker program. However, their results are mandatory baseline information as absolute cell counts for further investigations.

Blood samples are planned to be taken in the context of study inclusion and before any therapeutic intervention, and serve as baseline controls. Furthermore, second blood samples are collected in group A on cycle 1, day 8 (visit 2) after completion of radiotherapy to assess early radiogenic immune response in combination with nivolumab. The second blood sample in group B is also collected on cycle 1, day 8 (visit 2) to assess early nivolumab-related immune response without radiotherapy. A third blood sample will be taken for both groups on cycle 3, day 1 (visit 4), when radiotherapy is completed in group A and when all patients (groups A and B) have received two doses of nivolumab. A fourth and final blood sample will be collected for both groups either on cycle 7, day 1 or upon end of treatment, whichever occurs first.

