
### Study procedures

This study will enroll patients with metastatic non-squamous NSCLC suitable for 2nd-line and 3rd-line treatment. Study subject may have a necessity for radiotherapy of a metastatic site (study group A) or not (group B).

This is an open-label, two-group study. During screening and after written informed consent, patients will be stratified to either the radiotherapy/nivolumab treatment (group A) or nivolumab only treatment (group B), depending on necessity of radiation of a metastatic site.

An overview of all study procedures is presented in Table 2. For each patient enrolled, an electronic case report form (eCRF) must be completed by the principal investigator or authorized delegate from the study staff. This also applies to records for those patients who fail to complete the study. If a patient withdraws from the study, the reason must be noted in the eCRF. Subjects who are permanently discontinued from the study medication will be followed for safety unless consent is withdrawn or the subject is lost to follow-up or enrolled in another clinical study. All subjects will be followed for survival. Subjects who decline to return to the site for evaluations will be offered follow-up by phone every 3 months as an alternative.

**Table 2 Tab2:** Schedule of assessments

Procedure/Point in Time		Screening	Treatment				Follow-up	
		Inclusion	Cycle 1		Every further cycle (q2w)	End of treatment	Safety follow-up	Survival follow-up
			Day 1	Day 8				
Informed consent, eligibility criteria, demographics, medical and disease history		x						
FFPE tumor tissue (PD-L1)		x						
Vital signs, physical examination, ECOG		x	x	x	x	x	x	
Hematology, serum chemistry, liver function tests		x	x	x	x	x	x	
HBV, HCV		x						
Thyroid function test		x	x		x ^a^	x	x	
Pregnancy test		x			x ^a^			
AEs/SAEs		x	continuously				x	
Concomitant medication		x	continuously				x	x
QoL		x	x		x ^b^	x	x	x
Biomarker sample		x		x	x	x		
Radiographic tumor assessments		x			x ^a^		x	x
Survival information, subsequent therapies								x
Group A	Nivolumab		x		x			
	Radiotherapy		x	(x)				
Group B	Nivolumab		x		x			

^a^: every 3rd cycle (every 6 weeks)

^b^: every other cycle (every 4 weeks)

Data management and data quality assurance are conducted following the Standard Operational Procedures of the Institut für Klinische Forschung (IKF) (Frankfurt, Germany).

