#### Immunotherapy

Nivolumab will be given every two weeks at a dose of 240 mg to be administered as a 60 min IV infusion. Treatment regimen depends on study group: in study group A, nivolumab will be given on day 1 of the first cycle and continued to be given every two weeks. The first fraction of radiotherapy has to be delivered within 72 h after cycle 1 day 1.

In study group B, nivolumab will be given on day 1 of the first cycle and continued to be given every two weeks.

In both groups, nivolumab treatment will be continued until progression or until limiting toxicities occur.

Nivolumab administration will be delayed in case of any AE, laboratory abnormality or intercurrent illness which, in the judgment of the investigator, warrants delaying the dose of study medication.

Subjects may continue to receive treatment beyond confirmed progression in the absence of clinically significant deterioration and if investigators expect continual benefit from the treatment. For statistical analyses, these subjects will be considered to have investigator-assessed progressive disease at the time of the initial progression event.

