#### Radiotherapy

Radiotherapy planning will be based on computed tomography (CT) images with minimal 5 mm slices. For robust and reproducible patient positioning during both planning and treatment, all positioning aids (e.g. masks, cushions, vacuum beds) are allowed.

For irradiation, tumor lesions in all non-cerebral/non-pulmonary locations can be included if radiotherapy is indicated and prescribed according to common good clinical practice (e.g. bone, soft tissue, lymph nodes). Internal organ metastases (such as in liver, pancreas, adrenal glands) or brain metastases should not be irradiated. Patients with thoracic lesions (e.g. thoracic spine, chest wall) or mediastinal lymph nodes will be included if the planning target volume (PTV) for irradiation does not directly intersect with the contoured lungs.

Gross tumor volumes (GTV) are contoured on the planning CT, considering additional co-registered imaging techniques such as magnetic resonance imaging (MRI) or positron emission tomography (PET), if available. Derived from the GTV, clinical (CTV) and planning target volumes (PTV) are created using common institutional margins to confidently cover radiation targets and simultaneously spare organs at risk (OAR). Contouring of relevant OAR is only necessary in cases of close vicinity or anticipated critical radiation exposure. In case of thoracic target volumes, both lungs will be contoured to monitor lung dose exposure, which is required to be as low as reasonably achievable. In cases of subtotal lung registration, the OAR “both partial lungs” will be generated.

Radiation delivery must be planned 3D-conformally and CT-based with either photons or electrons including step-and-shoot/helical/volumetric intensity-modulated, stereotactic or conventional techniques using linear accelerators. Radiotherapy is delivered on workdays in 5 single fractions of 4 Gy up to a total dose of 20 Gy. Therefore, radiotherapy is expected to last no longer than 2 weeks. Dose specification follows the requirements of the reports 50, 62, and 83 of the International Commission of Radiation Units and Measurements.

Adequate patient positioning and correct isocenter localisation are verified radiologically making use of either kV/MV-cone/fan-beam-CTs or conventional X-ray-documentation of either isocenter or radiation fields. If positioning corrections are necessary, they must be documented in the radiotherapy protocol.

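### The group A day-8 blood sample is described as taken after radiotherapy, but the permitted schedule lets radiotherapy run past day 8

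*Protocol article*

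**What the plan says.** Four places in the protocol article bear on this.

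- **Blood collection** fixes the time and the meaning of the sample: "second blood samples are collected in group A on cycle 1, day 8 (visit 2) after completion of radiotherapy". Its purpose is "to assess early radiogenic immune response in combination with nivolumab". Group B is also sampled on cycle 1 day 8, to show the early nivolumab effect without radiotherapy. The third sample, in both groups, is on cycle 3 day 1, and the text notes that radiotherapy is finished in group A by then.
- **Immunotherapy** sets the start window: "The first fraction of radiotherapy has to be delivered within 72 h after cycle 1 day 1".
- **Radiotherapy** sets the course: "Radiotherapy is delivered on workdays in 5 single fractions of 4 Gy up to a total dose of 20 Gy". It adds that "radiotherapy is expected to last no longer than 2 weeks".
- **Table 2** (Study procedures) shows group A radiotherapy with a plain cross under day 1 and a bracketed cross under day 8.

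**The concern.** The sample is pinned to a calendar day and, in the same sentence, to the end of a course whose last day is not fixed. The start can slip by up to three days, and most five-workday courses cross a weekend. The bracketed mark in Table 2 shows that irradiation on day 8 was foreseen.

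Neither reading of the sentence resolves this. If the clause describes day 8, it is untrue for patients still under treatment. If it is a condition for drawing the sample, those patients cannot meet it on day 8.

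What is at stake is the meaning of one exploratory time point. If every group A day-8 sample is analysed as post-radiotherapy, patients sampled mid-course are pooled with patients who finished a day or more earlier. Any comparison with the group B day-8 samples is then blurred by differing exposure, and some samples carry the wrong label.

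**Working it through.** **Inputs from the article.** First fraction on study days 1 to 4 (the 72 h window, Immunotherapy); five fractions on workdays (Radiotherapy); draw on day 8 (Blood collection).

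**Assumptions.** Infusion on a weekday, one fraction per workday, no public holiday or interruption.

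**Formula.** Let *s* be the study day of the first fraction.
- Monday start: no weekend is crossed, so the last fraction is on day *s* + 4.
- Any other workday start: one weekend is crossed, so the last fraction is on day *s* + 6.

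**The plan's own figure first.** The course spans 5 calendar days (Monday start) or 7 (any other start). This agrees with the stated expectation of at most 2 weeks.

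**Study day of the last fraction** (a dash means the start would fall on a weekend):

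| Infusion (day 1) | Start day 1 | Start day 2 | Start day 3 | Start day 4 |
|---|---|---|---|---|
| Monday | 5 | 8 | 9 | 10 |
| Tuesday | 7 | 8 | 9 | 10 |
| Wednesday | 7 | 8 | 9 | – |
| Thursday | 7 | 8 | – | – |
| Friday | 7 | – | – | 8 |

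Permitted schedules: 4 + 4 + 3 + 2 + 2 = 15.

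| Last fraction | Schedules | Fractions given before day 8 | Is a day-8 draw after the course? |
|---|---|---|---|
| Day 5 or 7 | 5 of 15 | 5 | Yes |
| Day 8 | 5 of 15 | 4 | Only if drawn after that day's fraction |
| Day 9 or 10 | 5 of 15 | 2 or 3 | No |

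The 2 or 3 in the last row come from counting workdays before day 8. A day-3 start leaves days 3 to 7, which is 5 − 2 = 3 workdays. A day-4 start after a Monday or Tuesday infusion leaves days 4 to 7, which is 4 − 2 = 2.

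**When is the course finished before day 8?** A non-Monday start needs *s* + 6 ≤ 7, so *s* = 1. A Monday start needs *s* + 4 ≤ 7, so *s* ≤ 3; with *s* = 2 or 3 the infusion would have been on a Sunday or Saturday. For weekday infusions, then, only a day-1 start finishes before day 8.

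**Sensitivity.**
- Weekend infusions admitted: 20 schedules, of which 7 end before day 8, 5 on it and 8 after it.
- One public holiday during a day-1 course can move its last fraction to day 8.

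**Third sample.** At two-week cycles, cycle 3 day 1 is day 1 + 2 × 14 = day 29. The latest uninterrupted finish is day 10. A day-4 start using the full 14 days would end on day 4 + 13 = 17. The third sample therefore follows radiotherapy in every case.

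**The case against.** The strongest reply is that this is mainly a wording mismatch, and that several stronger readings fail.

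- *A reader might infer that the day-8 draw often falls during radiotherapy.* The article gives no distribution of start days. The plain mark at day 1 and the bracketed mark at day 8 in Table 2 suggest that a day-1 start is the norm, and all five such schedules finish in time. This stands: the share of patients affected could be small or large.
- *A reader might infer that 10 of 15 schedules conflict.* The text asks for a draw on day 8 after the course, not for a course finished before day 8. A draw later that day satisfies it when the last fraction is on day 8. This stands: the certain conflict is 5 of 15.
- *A reader might infer that day 8 is the main early readout.* No section ranks it so, and T-cell receptor sequencing uses only baseline and the end-of-study time point. This stands.
- *Draw windows and covariates for exploratory assays usually sit in the full protocol, laboratory manual or SAP.* True, and their absence here is no finding. But the point is a statement that conflicts with other statements in the same article, and unseen detail does not make it correct.
- *A clean post-radiotherapy sample already exists at cycle 3 day 1.* True. It limits the damage but does not correct the day-8 label.

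**Conclusion.** The contradiction holds in a limited form. Among 15 permitted weekday-infusion schedules, the description of the day-8 sample is true in 5, depends on the hour of the draw in 5, and is false in 5. In the last group only two or three of the five fractions precede the draw day. This rests on one fraction per workday, which is the natural reading, and on no interruption. The counts weight every permitted schedule equally and say nothing about the proportion of patients.

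The effect is confined to one of four time points in a voluntary, exploratory blood programme. The binomial test of the response rate, the 50 patients it requires, the secondary endpoints, the safety analysis and the third blood sample are untouched. A reader might infer a threat to the trial's main conclusions; nothing in the article supports that.

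**What to change.** Reconcile Blood collection, Immunotherapy, Radiotherapy and Table 2, leaving the radiotherapy schedule and the visits as they are.

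1. In Blood collection, delete the clause that places the group A day-8 draw after the end of radiotherapy. Describe it as a fixed-time sample on cycle 1 day 8, as in group B.
2. Classify each group A day-8 sample by the number of fractions delivered before the draw (course complete or ongoing), and use this in the day-8 analysis. A blanket label of on-radiotherapy should be avoided, since it would mislabel patients who had finished.
3. Name cycle 3 day 1 as the first time point at which all of group A is past radiotherapy.

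**Cost.** No extra samples or visits. Fraction dates and draw dates must be linked, and for draws on a fraction day their order must be known. The article does not say that these are captured. With 94 patients included by August 2019, part of the linkage would be retrospective, and some samples may have to be classed as unknown. The subset that is truly post-radiotherapy on day 8 will be smaller than all of group A.

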### Study endpoints

#### Primary endpoint

The primary endpoint will be the objective response rate (ORR) according to RECIST criteria 1.1.

#### Secondary endpoints

Secondary endpoints will be:
PFSPFS and ORR using assessment according to irRECISTOS1-year OS rateDescriptive sub-group analyses of efficacy in relation to PD-L1 expression levels (e.g. cut-off 1, 5, 10%)Treatment emergent adverse events according to common terminology criteria for adverse events (CTCAE) version 4.03Frequency of abnormal laboratory parametersQuality of Life [FACT-L, validated in [21]

#### Exploratory endpoints

Radiation-induced tumor-specific immune effects can explain events of tumor regression upon radiation treatment both within and beyond the irradiated fields and the immune system can be further stimulated by administration of a PD-1 blocking antibody such as nivolumab. The translational research accompanying this trial aims to elucidate the synergistic, immunostimulatory effects of radiotherapy and checkpoint inhibition that underlie these observations by covering the following aspects.

##### Exploratory analysis on radiation planning and dose administration

Exploratory analysis on radiation planning and dose administration will help to substantiate the phenomenon of radiation-induced abscopal effects. It will improve the option of radiation triggered systemic response through identification and possible prediction of both eligible targets for irradiation and probable lesion of abscopal response. To this end, both the location and composition of radiation targets and the anatomical profile of abscopally responding lesion must be carefully studied.

The following endpoints will address these questions:

Radiation oncology endpoints:
Specific anatomical location of irradiated targetsSpecific characteristics and composition of irradiated targets (e.g. bone metastasis [met.] vs. soft connective tissue met. vs. soft parenchymatous tissue met. vs. lymph node met.)Absolute size of GTV, CTV and PTVDose-volume histogram parameters such as D2%, D50%, and D98% within the PTVRadiation technique (e.g. 3D conventional vs. intensity-modulated radiotherapy) and beam energy

Radiology endpoints:
Specific anatomical location of abscopally responding target lesionsSpecific characteristics and composition of abscopally responding target lesions (e.g. bone metastasis [met.] vs. soft connective tissue met. vs. soft parenchymatous tissue met. vs. lymph node met.)Characteristics of abscopal response (size reduction [RECIST] vs. tissue density vs. contrast enhancement/perfusion vs. other signs of response)

##### Exploratory analysis on tissue samples

Tumor PD-L1 assessments will be performed as part of the clinical study. The results will be used both retrospectively for patient sub-grouping and within the biomarker program for correlation analysis. The PD-L1 IHC 28–8 pharmDx assay will be used.

In addition, the immune infiltrate associated with the tumor will be analyzed to identity different subsets of immune cells. To this end, tissue slides will be subjected to a panel of IHC markers capable of identifying various types of immune cells. Depending on the availability of tumor material, tissue samples will also be analyzed with respect to microsatellite instability.

##### Exploratory analysis on blood samples

Blood samples that are collected at different time points will be used to characterize the immune response and investigate biological processes before, during and after the administration of the treatment. Briefly, phenotypic fluorescence activated cell sorter (FACS) analysis will be used to analyze whole blood samples with respect to the changes in the T-cell composition. Furthermore, specific T-cell responses to a panel of putative lung cancer-associated antigens will be measured by IFN-γ enzyme linked immunospot technique using frozen peripheral blood mononuclear cells. T-cell receptor sequencing will be performed for 2 visits per patient (baseline and end of study time point), in order to elucidate whether and, if so, which of the T-cell clones will be expanded during treatment. Abundances of immunostimulatory cytokines will be quantified by measuring serum cytokines. Finally, changes in lymphocyte gene signature arising from the synergistic treatment of patients with radiotherapy and nivolumab will be monitored by mRNA expression profiling using mRNA isolated from whole blood and using the human HT-12 v4 Expression BeadChip Kit.

### Statistical analysis

#### Sample size calculation

The primary endpoint will be the ORR according to RECIST criteria 1.1. Based on the results from the Checkmate 057 trial (ClinicalTrials.gov Identifier: NCT01673867; [5]), the ORR in group B is assumed to be 19%. Moreover, in the population with high PD-L1 expression (PD-L1 > 10%) an ORR of 37% was observed [5]. It is hypothesized that by combining nivolumab and radiotherapy an ORR of 35% can be achieved in both PD-L1-negative and -positive patients.

The study requires *n* = 50 subjects (in group A) to detect whether the responding proportion (ORR) is higher than 19% by applying a binomial test at a one-sided significance level of 0.05 with a probability of 1-beta = 0.8, assuming an actual response rate of 35%.

Due to the fact that a retrospective PD-L1 analysis will be crucial to reach the study objectives, the PD-L1 status should be available for at least 50 patients per treatment group. Practical experiences indicate that at a rate of 20–30% tumor tissue samples do not contain sufficient material for a PD-L1 IHC assessment. By taking this and also potential patient dropouts into account, the total number of patients enrolled will be *n* = 65 per group to ascertain the required sample number for the PD-L1 sub-group analysis and to achieve a sufficient statistical power for the primary analysis in case of patient dropouts.

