### Study setting

The FORCE trial is a multicenter trial recruiting patients from 16 sites across Germany. A full list of sites can be obtained at clinicaltrials.gov (NCT03044626). Recruitment started in March 2017 (First Patient In) and will be completed in December 2019. As of August 2019, 104 patients have been screened, of whom 94 have been included in the trial. Overall, data from 100 participants (50 patients per treatment arm) are expected to be available for statistical analysis.

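### Enrolling 65 per group does not secure PD-L1 status in 50 per group: at the plan's own 20–30% tissue failure, 45.5 to 52 are expected

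*Protocol article*

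**What the plan says.** The relevant paragraph is in the Protocol article, Sample size calculation. It treats the retrospective PD-L1 analysis as crucial and sets a target: "the PD-L1 status should be available for at least 50 patients per treatment group". It then gives the expected loss: "Practical experiences indicate that at a rate of 20–30% tumor tissue samples do not contain sufficient material for a PD-L1 IHC assessment". The enrolment figure is presented as the consequence. "By taking this and also potential patient dropouts into account", the plan enrols "65 per group to ascertain the required sample number for the PD-L1 sub-group analysis", and also to protect the power of the primary analysis against dropout. No dropout rate and no inflation formula are shown.

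Three other places bear on the point:

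- **Study setting** gives a later forecast: "data from 100 participants (50 patients per treatment arm) are expected to be available for statistical analysis".
- **Table 1** requires a tissue block or at least 15 slides at entry. Under **Tissue collection**, the central laboratory judges afterwards whether the material is sufficient, and the sponsor may then ask for further archived tissue where any exists.
- **Secondary endpoints** and **Methods of statistical analysis** both label the PD-L1 subgroup work descriptive, with example cut-offs of 1, 5 and 10%.

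**The concern.** The target, the loss rate and the enrolment figure stand in one paragraph, and the third does not follow from the first two. A reader will take 50 patients with PD-L1 status per group as assured, with room left for dropout. On the plan's own rate that is so, in expectation, only near the favourable end of the range.

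The PD-L1 requirement is one of the two reasons given for enrolling 65 rather than 50 per group. The section also hypothesises a 35% response rate in both PD-L1-negative and PD-L1-positive patients, and the descriptive subgroup analysis is where that will be looked at. The number available for it should be stated correctly.

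**Working it through.** **Inputs, all from Sample size calculation.** Target: 50 with PD-L1 status per group. Tissue failure rate f: 20–30%. Enrolment: 65 per group. The check treats f as the share of patients left without a result and counts no recovered tissue and no dropout.

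**1. The base figure of 50 reproduces.** The plan sizes the radiotherapy group as follows: "to detect whether the responding proportion (ORR) is higher than 19% by applying a binomial test at a one-sided significance level of 0.05". It asks for power 0.8 at a true rate of 35%. In an exact binomial test with n = 50, success at 15 or more responses has a type I error of 0.0411 under 19% and power 0.812 under 35%. At n = 49 the power is 0.785, and 50 is the smallest n that reaches 0.80.

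**2. Where 65 may come from.** 50 × (1 + 0.30) = 65 exactly. This suggests that 30% was added to 50, when 50 should have been divided by 0.70. No formula is shown, so this is an inference, and the result below does not depend on it.

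**3. Yield from 65, the number needed, and the chance of success.** The expected yield is 65 × (1 − f). The number needed for an expected yield of 50 is 50/(1 − f), rounded up. The chance is P(X ≥ 50) with X binomial(65, 1 − f).

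| Failure rate f | Expected yield from 65 | Needed for 50 | Chance of at least 50 in one group |
|---|---|---|---|
| 20% | 65 × 0.80 = 52.0 | 50/0.80 = 62.5, so 63 | 78% |
| 25% | 65 × 0.75 = 48.75 | 50/0.75 = 66.7, so 67 | 42% |
| 30% | 65 × 0.70 = 45.5 | 50/0.70 = 71.4, so 72 | 14% |

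**4. Break-even.** 1 − 50/65 = 0.231. Above 23.1% failure the expected yield is below 50. That is (30 − 23.1)/(30 − 20) = 69% of the quoted range, including its midpoint. At 20% the margin is 52 − 50 = 2 patients.

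**5. The forecast in Study setting.** If its 50 patients per arm are counted before tissue failure, the number with PD-L1 status would be 50 × 0.80 = 40 down to 50 × 0.70 = 35. If they are counted after tissue failure, the forecast agrees with the target. The text does not say which is meant.

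**6. Primary test at 65.** Success at 19 or more responses has a type I error of 0.0305 and power 0.866. Tissue failure does not enter this calculation.

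**The case against.** **The rate is per sample, and tissue can be re-requested.** The 20–30% refers to samples. The protocol lets the sponsor ask for more archived material and encourages sites to send archival tissue alongside a recent biopsy. Patient-level failure could therefore be lower. This stands as a limit: the yields and probabilities above are before any recovery. It does not rescue the claim, because recovery depends on tissue existing, is given no size, and is not mentioned in the sample size reasoning. The entry criterion does not close the gap either, since it asks for a block or slides and not for adequate tumour content.

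**65 is enough at 20%.** True in expectation, but the plan quotes 20–30%, and even at 20% one group misses 50 with a probability of 22%.

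**The analysis is only descriptive.** This is correct and it limits the severity. No PD-L1 test, significance level or decision rule rests on the 50.

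**Stronger readings that the document does not support.**

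- A reader might infer that dropout makes the shortfall worse. No dropout rate is given, and the schedule of assessments collects the tissue at screening, so a patient who later drops out can still have a PD-L1 result.
- A reader might take 35–40 as the number now expected. That holds only if the 50 per arm in Study setting are counted before tissue failure.
- A reader might conclude that the protocol promises a subgroup precision it will not deliver. It states no subgroup interval width. If width scales with 1/√n, 45.5 in place of 50 gives √(50/45.5) = 1.048, about 5% wider.

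**Conclusion.** The claim that 65 per group ascertains 50 with PD-L1 status is wrong as written. At the plan's own failure rate the expected number is 52 at 20%, about 49 at 25% and 45.5 at 30%, so the largest expected shortfall is 4.5 patients per group. The target is met in expectation only up to 23.1% failure.

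This rests on two assumptions: that the sample-level rate applies to patients, with no tissue recovered on re-request, and, for the probabilities, that failures are independent between patients.

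Severity is minor to moderate. A reader might infer that the trial is underpowered or needs more patients. The document does not support that: the primary test uses all of group A regardless of PD-L1 status, and its exact power is about 81% at 50 patients and 87% at 65. Only the descriptive PD-L1 subgroup analysis is affected.

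**What to change.** In Sample size calculation, replace the statement that 65 per group secures the PD-L1 number with wording such as:

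*At a tissue failure rate of 20–30%, about 45–52 of 65 patients per group are expected to have PD-L1 status, before any tissue recovered on re-request.*

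In Study setting, say whether the 50 patients per arm expected for analysis are counted before or after tissue failure. If before, add that 35–40 per arm would then have PD-L1 status.

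The cost is two sentences of text and a less favourable stated number for the PD-L1 analysis. Enrolment, the primary test and its power stay as they are, and no extra patients are needed.
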